### Methods: participant timeline

Details for the schedule of enrolment, interventions and assessments of this study is depicted in Fig. 3.

**Fig. 3 Fig3:**
[figure not shown]
Schedule of enrolment, interventions, and assessments

### Week 0 (visit 1)

This is the initial baseline visit in which the parent and child are both present. It will take approximately 1 hour. After the researcher has outlined the trial and the potential risks and the parent and child both understand what participation involves, informed consent is obtained. At the baseline visit, a CRF will be firstly be completed by researcher in consultation with the parent. The parent and child will both independently complete the PinQ questionnaire at separate desks. The researcher will then explain the eDiary to the parent and help them save the eDiary link on their smartphone and give them a paper version if they are unable to use their phone. The next visit will be scheduled for 4 weeks’ time (Week 4) and will be booked at this appointment. The researcher will contact the parent after 1–2 days of commencing the intervention. This is over the phone or email to assess the participant for any initial potential adverse or allergic reaction.

### Week 2 (phone call only)

The researcher will call the parent to check adherence with the intervention and the diary as well as adverse reactions and changes to concomitant medications.

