**Safety (Week 4 and Week 8)**

Secondary outcomes in Stage 1 will include on the safety of the herbal formulation in children aged 6–14 years at Weeks 4 and 8 of the study. Data will be collected from adverse reactions (type, severity, relation to investigational product), and side effects experienced by the participant recorded in the diary. An interim analysis will be conducted after enrolment of 30 participants to assess safety and continuation of the trial. Also at this time point, a power calculation to confirm participant numbers needed to reach statistical significance will determine the total number of participants required for recruitment. Safety data will be continued to be collected throughout Stage 2.

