##### Case report form

The Case Report Form (CRF) will be completed by the researcher at weeks 0, 2, 4, 6, 8, 16, 24, and 32. The baseline data collection will include demographic data, height and weight measurement, medications including complementary and over the counter medicines they are taking, medical history, risk factors for NE, prior treatments for NE, continence history, fluid intake per day. There is ongoing data collection fortnightly of any adverse events or concomitant medication via phone call or clinic visit whilst taking the intervention. As part of the CRF, a quality of life questionnaire (PinQ) will be completed by both the participant and parent/guardian at baseline, week 4, 8 and 32. The quality of life questionnaire chosen is the Paediatric Quality of Life Questionnaire (PinQ).

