##### Diary

The daily diary for the first 8 weeks will constitute questions covering three main areas: compliance, fluid intake, and continence. There will be the option for the participant to complete it as an electronic diary or as a paper based one. This is for ease of the participant in their own environment. In the case of the electronic diary, the researcher will set up a widget on the parent’s smartphone. This is a link that takes the participant directly to their individual eDiary (which is identical to the paper one) where the parent is required to fill it in daily. Each participant will have an individual link which is linked to their own data within the online survey platform (Survey Gizmo). From week 9 to week 32, a weekly diary entry instead of daily will be required to record any weekly events of nocturia. This will be made available as an eDiary or a paper-based diary depending on the parent/guardian.

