### Week 4 (visit 2)

The first bottle of capsules are returned at this visit to allow the researcher to count and record remaining intervention for confirmation of adherence. Those parents who chose to complete the paper diary will also return the completed diary. Any adverse events and concomitant medications will be noted and actioned if required. The PinQ will be completed by the parent and the child and the researcher will collect day-time continence data about the impact of the capsule on any day symptoms. Another 4 weeks supply of the capsules will be dispensed to the participant. It is anticipated this visit will take 30 min. The next visit will be scheduled for another 4 weeks (Week 8).

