### Weeks 16 and 24 (phone call only)

The RA will contact the parent to check for any adverse reactions or concomitant medications, ask follow up questions for day time continence, and check diary compliance.

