### Week 32 (visit)

The parent and child will attend the college for one final visit. The RA will finally check for any adverse reactions and concomitant medications, ask follow up questions for day time continence, and check diary compliance. The parent and child will complete the PinQ for a final time and paper diaries submitted if necessary.

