### Monitoring

Minimal side effects were noted from the Urox trial in adults, with two episodes of diarrhoea, two urinary tract infections and one episode of flatulence. There were numerous side effects in the Placebo group; urinary tract infection, diarrhoea, headache worsened asthma, worsened memory, facial flushing, halitosis and worsened arthritic pain [30]. The Safety Summary for the product is available upon request. Safety data on side effects and adverse events associated with the intervention will be closely monitored and reported.

The Patient Information Sheet outlines that the parent / carer is able to phone the Researcher at any time if they feel that the child is experiencing an adverse reaction to the capsule. Parents are contacted via phone at 1–2 days after commencement of the capsule to determine tolerability and assess for potential adverse reactions. The electronic diary also provides parents with an opportunity to note any potential episodes of the child feeling unwell with an option to request the researchers contact them to further follow up. The researcher will determine if the reaction is an adverse event (AE) or a serious adverse event (SAE) and follow the adverse event flow chart (see Fig. 4). All AEs are also noted in the Adverse Events Log and individual participant case report form.

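### Terms for harm and descriptions of the diary are inconsistent, so events not attributed to the capsule may be under-collected, mainly after Week 8

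*Protocol article*

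**What the plan says.** Safety is a secondary outcome. The *Safety (Week 4 and Week 8)* section names two sources: adverse reactions, recorded with type, severity and relation to the product, and "side effects experienced by the participant recorded in the diary". It adds that safety data go on being collected throughout Stage 2.

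The *Case report form* section gives a general rule for the treatment period: "There is ongoing data collection fortnightly of any adverse events or concomitant medication via phone call or clinic visit whilst taking the intervention".

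The contact descriptions vary:

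- Week 2 call: the researcher is to "check adherence with the intervention and the diary as well as adverse reactions and changes to concomitant medications". The Week 6 call is worded the same way.
- Week 4 visit: "Any adverse events and concomitant medications will be noted and actioned if required". The Week 8 visit uses the same sentence.
- Weeks 16 and 24: "The RA will contact the parent to check for any adverse reactions or concomitant medications".
- Week 32: "The RA will finally check for any adverse reactions and concomitant medications".

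On the diary, the *Diary* section describes "questions covering three main areas: compliance, fluid intake, and continence" for the first 8 weeks and calls the electronic and paper versions identical. From Week 9 it describes a weekly entry for nocturia. The *Monitoring* section says: "The electronic diary also provides parents with an opportunity to note any potential episodes of the child feeling unwell", with an option to ask the researchers to make contact.

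The *Termination criteria* section defines an adverse event by hospitalisation, threat to life, death or disability.

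**The concern.** In a blinded placebo-controlled trial, harm is best shown by comparing all untoward events between arms and judging their relation to the product afterwards. If a contact asks only about reactions, a parent or research assistant may leave out an event that nobody suspects the capsule of causing. An unexpected effect is exactly the kind that nobody suspects. The *Statistical methods* section plans safety tables by treatment group at the interim analysis and at the end of the trial. Those tables can be no more complete than the questions behind them.

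The diary is the second safety source. If staff cannot tell from the plan whether it has a place for side effects, or whether the paper version has one too, this source may differ between families according to the format they chose.

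**Working it through.** The plan states no figure on this point, so the check is a count of wording followed by a comparison of sections.

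**Step 1: term used at each scheduled contact after baseline.**

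| Contact | Term in the contact description | On treatment? | Covered by the fortnightly rule in *Case report form*? |
|---|---|---|---|
| Week 2 | adverse reactions | yes | yes |
| Week 4 | any adverse events | yes | yes |
| Week 6 | adverse reactions | yes | yes |
| Week 8 | any adverse events | yes | yes |
| Week 16 | adverse reactions | no | no |
| Week 24 | adverse reactions | no | no |
| Week 32 | adverse reactions | no | no |

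The narrower term appears at 5 of 7 contacts. The *Week 0 (visit 1)* section also describes a contact 1–2 days after starting, which looks for an adverse or allergic reaction. Counting it gives 6 of 8.

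**Step 2: what the general rule repairs.** The rule covers phone calls and visits while the child takes the capsule, so it includes Weeks 2 and 6. Those calls are described in two ways, but the wider description is in the plan. That leaves 5 − 2 = 3 contacts (Weeks 16, 24 and 32) with no such rule. They serve Weeks 9 to 32, that is 32 − 8 = 24 of the 32 weeks.

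**Step 3: other sources after Week 8.** The weekly diary is described for nocturia only. The *Monitoring* section says all adverse events are logged and entered on the case report form. That governs what happens to an event once it is known, not whether it is asked for. No section states that all adverse events are sought after Week 8, although safety collection is said to continue in Stage 2. The article does not define Stage 2. I take it to be the follow-up after Week 8, because the same section ties Stage 1 to Weeks 4 and 8.

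**Step 4: the diary.** Three sections do not fit together. *Safety* relies on side effects recorded in the diary. *Diary* lists three main areas, none of them side effects. *Monitoring* describes an entry for feeling unwell, but speaks of the electronic diary. If the two formats are identical, the paper diary should carry the entry too, but the plan does not say so. A contact request written on paper is not visible to staff until the diary comes back: at Week 4 or Week 8 on treatment, and at the end of the trial for the follow-up diaries.

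**Step 5: the word itself.** Adverse event is defined once, under *Termination criteria*, in the terms of a serious event. Elsewhere, *Monitoring* treats adverse event and serious adverse event as separate classes. Applied literally, the definition would shrink any adverse events to serious ones at Weeks 4 and 8 and in the fortnightly rule.

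**The case against.** The strongest answer is that adverse reaction is used loosely and not as a causal filter. The *Safety* section records each reaction's relation to the product, which would be redundant if relation were presumed. *Monitoring* has the researcher classify a reaction as an adverse event or a serious one, so reaction may simply mean the raw report. No section describes a parent or assistant screening by cause. This stands in part: it makes the term ambiguous. Yet *Monitoring* also invites parents to phone about a reaction to the capsule, which does attribute cause before reporting.

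It can also be said that the fortnightly rule and the open wording at Weeks 4 and 8 cover the treatment period, that the unwell entry needs no attribution, and that three main areas need not be a complete list. All of this stands. Parents may phone at any time, and the Week 2 and 6 calls check the diary, so a paper note is not the only route.

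A reader might infer from five of seven contacts that five sevenths of the events not blamed on the capsule are lost. The documents do not support that. It would require that staff ignore the fortnightly rule, that parents recall nothing at the next open question, and that events fall equally between contacts, although the intervals are 2 weeks on treatment and 8 weeks afterwards.

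A reader might also infer that the 40% termination criterion would be reached too early because unattributed events drop out of the denominator. That needs the same assumptions. It also sits badly with the section's own definition, since events as serious as those it lists are unlikely to go unreported because a call asked about reactions.

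Finally, the schedule and the adverse event flow chart are figures that are not available here, and exact call scripts are commonly left to the full protocol. They may settle the wording. The contradictions in the printed text remain.

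**Conclusion.** The point holds as an inconsistency to be reconciled, with a possible gap in collection after treatment. On treatment, the wording at Weeks 2 and 6 conflicts with the fortnightly rule, but all-cause collection is stated elsewhere and the practical loss may be nil. For Weeks 9 to 32, no passage states that all adverse events are asked for, so events not attributed to the capsule may be under-collected. This assumes that Stage 2 means the follow-up period and that staff could read adverse reaction in its narrower sense. The extent of any loss cannot be estimated from the documents.

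The diary sections do conflict, but it would go too far to say that the diary has no place for side effects, given the unwell entry under *Monitoring*. The serious-event definition under *Termination criteria* is part of the same problem, because it can narrow collection even where the text says any adverse events.

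**What to change.** - In the sections for Weeks 2, 6, 16 and 24, and 32, ask the same open question about any untoward event, serious or not and whatever the suspected cause. Judge relation to the product afterwards.
- Reconcile this with the definition under *Termination criteria*. Simply exchanging adverse reactions for adverse events, with that definition left as it is, could narrow collection to serious events.
- In the *Diary* section, state the unwell item for both the electronic and the paper format, in line with *Safety* and *Monitoring*.
- Tell families using paper to phone the researcher, because a written contact request is not seen until the diary is returned.

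The cost is some rewording of the contact descriptions and one diary item, plus slightly more unrelated minor events to log.

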### Week 4 (visit 2)

The first bottle of capsules are returned at this visit to allow the researcher to count and record remaining intervention for confirmation of adherence. Those parents who chose to complete the paper diary will also return the completed diary. Any adverse events and concomitant medications will be noted and actioned if required. The PinQ will be completed by the parent and the child and the researcher will collect day-time continence data about the impact of the capsule on any day symptoms. Another 4 weeks supply of the capsules will be dispensed to the participant. It is anticipated this visit will take 30 min. The next visit will be scheduled for another 4 weeks (Week 8).

### Week 6 (phone call only)

The RA will call the parent to check adherence with the intervention and the diary as well as adverse reactions and changes to concomitant medications.

### Week 8 (visit 3)

The child and parent will attend this final visit to deliver the remaining bottle of capsules and diary. The RA will count and record any remaining intervention. Any adverse events and concomitant medications will be noted and actioned if required. The PinQ will be completed by the parent and the child and the RA will collect data about day continence. They will be offered paper diaries to cover the period from Week 8 to Week 32 if they do not wish to use the ediary format, with a pre-paid envelope to send them back to the college at the end of the trial. The visit is anticipated to take 30 min.

### Weeks 16 and 24 (phone call only)

The RA will contact the parent to check for any adverse reactions or concomitant medications, ask follow up questions for day time continence, and check diary compliance.

### Week 32 (visit)

The parent and child will attend the college for one final visit. The RA will finally check for any adverse reactions and concomitant medications, ask follow up questions for day time continence, and check diary compliance. The parent and child will complete the PinQ for a final time and paper diaries submitted if necessary.

### Trial completion

The trial is completed for the participant and they will receive a thank you letter for their participation. If they have indicated on their consent form that they wish to receive a copy of the Summary of Findings, their name will be added to a list and they will be contacted when the findings have been published.

### Monitoring

Minimal side effects were noted from the Urox trial in adults, with two episodes of diarrhoea, two urinary tract infections and one episode of flatulence. There were numerous side effects in the Placebo group; urinary tract infection, diarrhoea, headache worsened asthma, worsened memory, facial flushing, halitosis and worsened arthritic pain [30]. The Safety Summary for the product is available upon request. Safety data on side effects and adverse events associated with the intervention will be closely monitored and reported.

The Patient Information Sheet outlines that the parent / carer is able to phone the Researcher at any time if they feel that the child is experiencing an adverse reaction to the capsule. Parents are contacted via phone at 1–2 days after commencement of the capsule to determine tolerability and assess for potential adverse reactions. The electronic diary also provides parents with an opportunity to note any potential episodes of the child feeling unwell with an option to request the researchers contact them to further follow up. The researcher will determine if the reaction is an adverse event (AE) or a serious adverse event (SAE) and follow the adverse event flow chart (see Fig. 4). All AEs are also noted in the Adverse Events Log and individual participant case report form.

**Fig. 4 Fig4:**
[figure not shown]
Adverse event flow chart

A Safety Advisory Board overseeing any serious adverse events (SAE) consists of three independent expert representatives (General Practitioner, Pharmacist and Herbal Medicine researcher and scholar). Any SAE’s will assessed by the safety committee with 24 h to determine if the adverse event is attributed to the interventional agent. The ensuing action will be decided between the Safety Advisory Board and the investigators.

In light of new information about the treatment that may arise during the trial, the participant / parent will be notified and it will be discussed with the parent whether they want the child / participant to continue on the trial. If it is decided that the participant will continue in the study, they will be asked to sign an updated consent form. Also, on receiving new information on potential harms, the researchers might consider it appropriate to withdraw specific a participant from the clinical trial. If this happens, the researcher will explain the reasons and arrange for the participant’s regular health care to continue by sending an updated letter to the child’s local medical practitioner.

An interim analysis will be performed on the primary endpoint when 30 participants have been randomised and completed 8 weeks of the intervention.. The interim-analysis will be performed by the PI, blinded for the treatment allocation. The results of the analysis will be discussed with the Safety Advisory Board and the research team in a joint meeting. A re-calculation of the total target sample will be applied based on the interim analysis, with any changes to final intended sample size reported to the ethics committees overseeing the conduct of the project.

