#### Trial duration

Each participation will be involved in the trial for 32 weeks. The overall flow of study involvement is reported in Fig. 2. The first 8 weeks involve the oral ingestion of the daily capsule. The post-interventional period involves weekly entry in the electronic diary recording any ongoing episodes of nocturia for 6 months to determine the long-term effects of the capsule on NE. There is also 2 monthly follow up phone calls to the note any new changes to medications or additional NE treatments as well as the daytime continence questions. A final visit to the clinic will occur at Week 32.

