#### Adherence

Adherence to the protocol will be measured by the number of capsules remaining at Week 8, as counted by the researcher. No participants will be excluded based on incomplete adherence to the protocol. Sensitivity analyses to control for variations in adherence will be controlled for in the analysis. Participants that seek other treatment at any stage during their involvement in the trial will be classified as treatment failures in the analysis.

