#### Ancillary and post-trial care

At the completion of the trial (after the 6 months of post monitoring), each child will receive two bottles of the Bedtime Buddy. Due to the blinding of the trial until after analysis, this allows those who may be on the placebo to have access to the investigational product. If any participant suffers psychological harm during the trial, counselling services will be provided for the child.

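### On new harm information, the protocol names withdrawal from the trial rather than stopping the capsules, so ending treatment is not separated from ending follow-up (minor, cheap to fix)

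*Protocol article*

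**What the plan says.** The clause is in the Monitoring section of the protocol article, in the paragraph on new information after the adverse event flow chart (Fig. 4).

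- **Parent's decision.** The family is told of new information, and "it will be discussed with the parent whether they want the child / participant to continue on the trial". A family that stays signs an updated consent form.
- **Researchers' action.** On new information about harms, "the researchers might consider it appropriate to withdraw specific a participant from the clinical trial". The researcher then explains why and writes to the child's local doctor so that ordinary care carries on. No further trial data collection is mentioned for that child.

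Other sections bear on it:

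- **Trial duration:** "The first 8 weeks involve the oral ingestion of the daily capsule". Total participation is 32 weeks.
- **Diary:** "From week 9 to week 32, a weekly diary entry instead of daily will be required".
- **Weeks 16 and 24; Week 32:** two calls and a final visit, each with an adverse-reaction check. The week-32 visit also includes the last quality-of-life questionnaire (PinQ).
- **Safety (Week 4 and Week 8):** safety data collection goes on through Stage 2.
- **Adherence:** "No participants will be excluded based on incomplete adherence to the protocol".
- **Statistical methods:** analysis is by intention to treat.
- **Ancillary and post-trial care:** product is supplied once more after week 32, in these terms: "At the completion of the trial (after the 6 months of post monitoring), each child will receive two bottles of the Bedtime Buddy". No exception for harm is stated.

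**The concern.** Two decisions are folded into one. Stopping the capsule protects the child from further trial dosing. Ending follow-up removes the child from observation. The clause names only the second, for researchers and parents alike, although the risk it responds to comes from the first.

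Two things are at stake. A child about whom there is a harm concern would lose the remaining scheduled adverse-reaction checks, and the trial would lose outcome data for a harm-related reason. Before week 8 that includes the primary outcome, which an intention-to-treat analysis needs. Stopping the capsules would give the same protection from trial dosing and keep those data.

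The post-trial supply is a linked detail. As written, a child whose capsules had been stopped for harm and who stayed to week 32 would still be given the active product.

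**Working it through.** There is no stated figure to reproduce. The check sets the clause against the schedule.

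**Inputs**

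- Capsules: weeks 1 to 8 (Trial duration; Table 1).
- Post-baseline contacts: 1–2 days after starting, then weeks 2, 4, 6, 8, 16, 24 and 32, which makes 8 (Week 0 to Week 32 sections; Monitoring).
- Daily diary: 8 × 7 = 56 entries. Weekly diary: weeks 9 to 32 = 24 entries (Diary).
- Post-baseline PinQ: weeks 4, 8 and 32, which makes 3.
- Primary outcome: week 8.
- Planned sample: 80, allocated 1:1, with 20% attrition allowed for (Sample size; Trial design).

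**Step 1: overlap of hazard and follow-up.** The capsule-free part of participation is 32 − 8 = 24 weeks, and 24/32 = 75%.

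**Step 2: what one withdrawal forgoes.** These are illustrations. The protocol does not say when, or whether, the clause would be used.

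| Withdrawn just after | Contacts lost | Daily entries lost | Weekly entries lost | PinQ lost | Primary outcome lost | Trial dosing days avoided |
|---|---|---|---|---|---|---|
| Week 2 | 6 | (8 − 2) × 7 = 42 | 24 | 3 | yes | 42 |
| Week 4 | 5 | (8 − 4) × 7 = 28 | 24 | 2 | yes | 28 |
| Week 8 | 3 | 0 | 24 | 1 | no | 0 |
| Week 24 | 1 | 0 | 32 − 24 = 8 | 1 | no | 0 |

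In every row, stopping any remaining capsules avoids the same number of trial dosing days and loses none of the scheduled data.

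**Step 3: scale.** One child is 1/(80/2) = 2.5% of an arm. The attrition allowance is 0.20 × 80 = 16 children, so one child uses 1/16 = 6.25% of it. How many children would be withdrawn under this clause cannot be derived from the protocol.

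**Step 4: post-trial supply.** Bottle size is not given. At the week-4 visit the first bottle is returned and "Another 4 weeks supply of the capsules will be dispensed to the participant". If a post-trial bottle also holds four weeks (an assumption), two bottles are 2 × 4 = 8 weeks of product, as long as the trial course. At two weeks per bottle it would be 4 weeks. The point does not depend on which is right.

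**The case against.** The strongest reply is that nothing is actually fixed. The clause is permissive and applies to individual children. The article condenses a fuller protocol, where rules on discontinuing treatment and on data after withdrawal usually sit. The flow chart that might cover stopping the product is not shown. The adherence rule already lets a child who stops capsules stay and be analysed, and safety collection continues in Stage 2. Withdrawing a child who has finished dosing would serve little purpose, so the later rows of the table may never arise. The supply of two bottles exists to give placebo children access, and reading it as an order to supply a harmed child is over-literal.

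Much of this stands, and it limits what can be concluded. A reader might infer more than the document supports:

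- *That a child whose capsules are stopped must leave.* The clause does not forbid staying, and the adherence rule would tolerate it.
- *That later harm would go unrecorded.* The Monitoring section says "the parent / carer is able to phone the Researcher at any time if they feel that the child is experiencing an adverse reaction". What would be lost is the scheduled checks.
- *That serious adverse events are handled this way.* Their management is left to the Safety Advisory Board with the investigators, which is a separate route.
- *That children will be withdrawn in weeks 9 to 32, or that the arms will lose children unequally.* Neither is shown. The investigators making the decision are blinded.
- *That sample size or the intention-to-treat analysis is undermined.* No stated figure changes.

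What does not stand is that this is mere silence. The article states an action and frames the parent's choice, and both are set at leaving the trial. That the clause does not say data collection ends is true. However, leaving the trial with hand-over to usual care is most naturally read that way, and nothing in the article says otherwise.

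**Conclusion.** The point holds as a minor design improvement. The only action named for the researchers on new harm information is withdrawal from the trial, and the only choice described for parents is to continue or not, so stopping the capsule is not separated from ending follow-up. A child withdrawn under the clause would lose whatever scheduled adverse-reaction checks and outcomes remain, including the primary outcome if this happens before week 8.

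The size is probably small. It rests on reading withdrawal from the trial in its ordinary sense, as the end of scheduled data collection, and on the full protocol and the flow chart not already providing for continued follow-up. The unqualified post-trial supply deserves a harm exception, but it is a secondary wording matter.

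**What to change.** **Monitoring, paragraph on new information.**

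- Make the researchers' action stopping the capsules.
- Offer parents three choices: continue; stop capsules and stay in follow-up; or leave the trial.
- Unless consent or assent to follow-up is withdrawn, keep the scheduled diaries, contacts, visits and PinQ to week 32.
- Record the reason for stopping, and analyse the child as randomised.
- If the information arrives after week 8, inform the family and continue follow-up on the same terms.

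**Ancillary and post-trial care.** Do not supply the bottles to a child whose capsules were stopped for harm, or where new harm information makes supply inappropriate.

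**Cost.** Wording changes in two sections and the matching consent text. Every contact involved is already scheduled. The downside is that some families go on completing diaries and contacts after capsules stop, and some children do not receive the bottles.
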